### Education of the Health Care Professionals Prior to the Intervention

A number of APNs will be educated to carry out MI, depending on funding and resources. They will be coached by trainers from the Motivational Interviewing Network of Trainers.

The theoretical and practical part of the education includes training in the key elements of MI, which is generally facilitated through eliciting change talk and exploring ambivalence about behavioral change while trying to examine discrepancies between the individual’s current behavior and core values or personal goals. The health care professionals will be introduced to MI methods including reflective listening and acknowledgement, so they will be able to clarify the patient’s goals and concerns, as well as elicit reasons for change using the patient’s own words. The role of the health care professionals is to coach and support the patients in discovering and developing their own resources for change and management at the patient’s request.

After the course, the health care professionals will be individually supervised by the MI trainer in 10 real patient situations. The supervision will include audiotaping and evaluation inspired by the Motivational Interviewing Treatment Integrity (MITI) coding system version 4.2.1 [33]. The MITI coding system is divided into a global rating and behavioral counts. The global rating is a 5-point Likert scale, where 1 indicates low competence in MI and 5 indicates high competence in MI. The behavior counts reveal MI behavior in proportion to all behavior, where a high percentage indicates a high competence in MI.

### Measurements and Outcomes

The primary outcome measure is HbA_1c_. Secondary clinical outcomes include systolic and diastolic blood pressure, weight, BMI, waist and hip circumference, and fasting blood samples (fasting plasma glucose, total cholesterol, triglyceride, high-density lipoprotein, and low-density lipoprotein). Additionally, secondary psychosocial and self-care behavior outcomes include: psychological distress (Kessler 10 [K10]; score range 10-50) [34], quality of life (QOL) (WHOQOL-BREF; domain score range 0-100) [35], diabetes self-care activities (Summary of Diabetes Self-Care Activities [SDSCA]; score range 0-7, representing number of days per week) [36], and diabetes management self-efﬁcacy (Chinese Diabetes Management Self-Efficacy Scale [C-DMSES]; score range 0-200) [37]. These surveys have been shown to demonstrate satisfactory psychometric properties.

K10 is a 10-item questionnaire intended to yield a global measure of distress based on questions about anxiety and depressive symptoms that a person has experienced in the most recent 4-week period.

The WHOQOL-BREF instrument comprises 26 items that measure the following broad domains: physical health, psychological health, social relationships, and environment. The WHOQOL-BREF is a shorter version of the original instrument that may be more convenient for use in large research studies or clinical trials. Both the self-administered and the interview version of the Hong Kong Chinese WHOQOL-BREF will be available [38].

The SDSCA measures frequency of self-care activity in the last 7 days for five aspects of the diabetes regimen: general diet (adherence to healthy diet), specific diet (ie, ate fruits and low-fat foods), foot care, blood-glucose testing, exercise, and taking recommended diabetes medication. Participants rate themselves from 0 to 7 on each item. The mean scores of the 11 items are then used to assess a participants’ self-care behavior.

C-DMSES assesses the extent that participants are confident they can self-monitor nutrition, blood sugar, foot exams, physical exercise, weight, and medical treatment. Participants rate themselves on an 11-point scale ranging from “0=can’t do at all” to “10=certain can do”. The mean scores of the 20 items are used to assess participants’ self-efficacy.

All patient level outcomes will be assessed at baseline, and again at 6 months and 12 months, during a clinical health check and an interviewer-administered questionnaire. All participants will be instructed to fast overnight for a minimum of 12 hours, and participant fasting times will be recorded prior to each blood test. When fasting times are insufﬁcient, participants will be asked to reschedule their appointment. Intervention and control groups will both undergo the same assessments, and all participants will be informed of their clinical results. Participants who are absent for outcome assessments will be contacted whenever possible by a phone call and asked to reschedule. Owing to the pragmatic nature of this trial, data collectors will not be blinded to group allocation; however, laboratory technicians will be blinded. Blood samples will be analyzed centrally at the Chemical Pathology Laboratories at Tuen Mun Hospital in Hong Kong.

### Fidelity

To externally verify that MI and usual care differ as expected, 2 out of 20 participants (10%) in both the MI and usual care sessions will be randomly selected for coding on adherence to MI principles using the MITI coding system by an expert independent coding group. Coders are blind to the study arm of the session and the study hypotheses. We anticipate that MI sessions will receive scores of 4 or higher on the 1 to 5 global rating and be significantly higher than usual care sessions on ratings of evocation, collaboration, empathy, and autonomous support. With respect to frequency measures for counselor behavior we expect MI sessions to have a higher reflection-to-question ratio and significantly fewer instances of giving information.

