### Sample Size Calculation

Sample size estimates were calculated using the ﬁxed number of clusters (2) available to the current study. The intracluster correlation coefﬁcient (ICC) accounts for the greater similarity of responses in patients within clusters compared with between clusters, and we could apply an ICC of 0.05 as typical in primary care settings [29]. The effect size for the primary outcome, HbA_1c_, was anticipated to be 0.32%, based on findings from a published meta-analysis [29]. Using these parameters, a sample size calculator for cluster-randomized trials [29] could estimate a total number of samples that would be required to achieve a power of 80%, while maintaining an alpha of 5% and a participant attrition rate of 20%.

However, since this is a pilot study, we will deploy a convenient sampling of 20 to 25 samples in each arm depending on resources. We anticipate performing a pragmatic cluster RCT in the future when resources are available so that sample size can be calculated with adequate power.

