### Research Intervention

The theoretical approach of the intervention is based on the self-efficacy theory and MI spirit. Perceived self-efficacy is defined as people’s beliefs about their capabilities of producing designated levels of performance on exercising influence over events that affect their lives [30]. MI is used as a method to facilitate this process and is a directive counselling style for eliciting behavior change by helping patients to explore and resolve ambivalence [31,32]. In addition to their usual care, patients in the intervention group will receive a 1-year MI program consisting of up to five individual counselling sessions lasting approximately 30 to 45 minutes. Each participant in the intervention group is assigned an APN who has received training in MI. The style of the interview is standardized with the following components: seeking to understand the person’s frame of reference; expressing acceptance and affirmation; eliciting and selectively reinforcing the client’s own self-motivational statements of problem recognition, concern, desire and intention to change, and ability to change; exploring the client’s degree of readiness to change; and affirming the client’s freedom of choice and self-direction. Exploring readiness to change is used as a component of the therapeutic process and not an outcome. Each session follows a semistructured MI format, specifically developed for this intervention program. Participants may bring up any concerning issues related to diabetes self-care during the intervention sessions. The participants in the intervention group may be referred by the health care professional to individual counselling for lifestyle modification, which may include dietary changes, promotion of physical activity, and counseling on quitting smoking and minimizing alcohol consumption.

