### Statistical Analysis

Descriptive statistics will be used to summarize the characteristics of the GOPCs and participants with regard to baseline characteristics and patterns of mean change over time. The primary analysis will examine the changes in HbA_1c_ at the 6- and 12-month follow-ups in comparison to the baseline. Secondary analyses will include all clinical, psychosocial, and self-care measures that are continuous outcomes. For data analyses, SPSS (IBM Corp, Armonk, NY) will be used. As this is a pilot study, nonparametric statistical tests will be used. The baseline values will be reported as means (SD). A *P*-value<.05 will be regarded as statistically significant.

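### With two participants coded per arm as the unit, an exact two-sided rank test cannot deliver the significant differences that the fidelity check expects

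*Protocol article*

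**What the plan says.** The Fidelity section of the protocol article gives the purpose of the check: "To externally verify that MI and usual care differ as expected". The sample is fixed in the same sentence: "2 out of 20 participants (10%) in both the MI and usual care sessions will be randomly selected for coding". I read this as two participants in each arm.

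The section then states what is anticipated. MI sessions should reach a global rating of 4 or more, and should "be significantly higher than usual care sessions on ratings of evocation, collaboration, empathy, and autonomous support". For behaviour counts, the reflection-to-question ratio should simply be higher, while MI should show "significantly fewer instances of giving information".

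The Statistical Analysis section says "As this is a pilot study, nonparametric statistical tests will be used" and that a P "value<.05 will be regarded as statistically significant". It names no separate test for fidelity.

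Two other sections bear on the numbers. Under Sample Size Calculation, "we will deploy a convenient sampling of 20 to 25 samples in each arm depending on resources". Under Research Intervention, MI participants receive "up to five individual counselling sessions lasting approximately 30 to 45 minutes". The article does not say how many sessions of each selected participant are coded, or how many recorded sessions a usual-care participant would have.

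**The concern.** The article fixes both the number of coded participants and the expected result, and the two do not fit together. A rank test on very few observations has a floor below which its P value cannot fall, however large the difference. With two per arm that floor lies far above .05.

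At stake is the meaning of what is offered as external verification that the arms received different care. As written, the report would carry one of two things. It could give a non-significant comparison that says almost nothing about delivery. Or it could give a significant one obtained by counting repeated sessions of the same few patients as independent. Neither verifies the contrast between the arms.

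**Working it through.** **Inputs.** Two of 20 participants per arm (Fidelity); nonparametric tests and a .05 threshold (Statistical Analysis); 20 to 25 participants per arm (Sample Size Calculation); up to five MI sessions per participant (Research Intervention). Assumptions: the general test rule also covers fidelity, and tests are two-sided (the article does not state sidedness).

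**The plan's own figure.** 2/20 = 0.10, so the stated 10% is right. With 25 per arm, two participants would be 2/25 = 8%, and 10% would be 2.5.

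**Participant as the unit.** With n per arm there are C(2n, n) equally likely rank arrangements under no difference. Complete separation is the most extreme result in each direction, so the smallest exact two-sided P is 2/C(2n, n).

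| Coded per arm | C(2n, n) | Smallest exact two-sided P |
|---|---|---|
| 2 | 6 | 2/6 = 0.333 |
| 3 (2.5 rounded up) | 20 | 2/20 = 0.100 |
| 4 | 70 | 2/70 = 0.029 |
| 5 | 252 | 2/252 = 0.008 |

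P<.05 first becomes possible at four per arm, and then only with complete separation.

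**Other versions of the test at two against two.**
- Exact one-sided: 1/6 = 0.167.
- Large-sample approximation, two-sided, no ties: 0.121 without and 0.245 with continuity correction.
- Large-sample approximation, two-sided, both scores tied within each arm: 0.083 without and 0.194 with correction.
- Only a one-sided, uncorrected approximation with fully tied scores falls below .05 (0.083/2 = 0.042). The approximation is not valid at this size, and the exact one-sided value is 0.167.

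At three against three, the uncorrected two-sided approximation can print 0.0495 (0.025 with full ties), but the exact value is 0.100.

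**A t-test.** It is not bound by the rank floor. At two against two it needs a standardized difference of about 5.7 for 80% power at two-sided .05, and it departs from the nonparametric rule.

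**Session as the unit.** Two MI participants with up to five sessions each give up to 2 × 5 = 10 sessions. Against two usual-care sessions (an assumed number), the floor is 2/C(12, 2) = 2/66 = 0.030, below .05. The ten sessions still come from two patients and the nurses assigned to them, so they are not ten independent observations and the calculation behind 0.030 does not hold.

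**The case against.** The strongest reply is that the article sets no fidelity test at all. It says what is anticipated and expected, and gives no pass or fail rule and no consequence. Its one numeric benchmark, a global rating of 4 or more, can be met with two participants, and the reflection-to-question ratio need only be higher. The Statistical Analysis section lists HbA1c and the clinical, psychosocial and self-care measures, not fidelity ratings, so carrying its test rule over is an inference. The unit is also open: participants are selected, but sessions are compared.

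Most of this stands, and it limits the point. A reader might infer that the check is bound to fail, or that its power is exactly zero. The documents do not support that, because they state an expectation rather than a decision rule and leave room for a session-level comparison. A reader might also infer that a non-significant result would be taken as poor delivery and would damage the reading of HbA1c. Nothing in the article says so. The section on educating the health care professionals describes further evidence on competence: supervision in 10 real patient situations with audiotaping and MITI-inspired evaluation.

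Two things do not rescue the wording. The article defines statistical significance itself, and within Fidelity it distinguishes items that should be higher from items that should differ significantly, so the word is not obviously casual. The session-level reading reaches .05 only by ignoring clustering within two patients per arm. Nor is this a detail left to a fuller document, since the article states both the sample and the expected significance.

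**Conclusion.** The point holds in a conditional form. With two participants per arm as the unit and an exact two-sided rank test, the smallest attainable P is 0.333, or 0.100 with three per arm. The significant differences expected on four ratings and on information giving cannot then be shown, even with complete separation. A session-level analysis could formally reach P<.05, but without valid support.

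This rests on reading the sample as two per arm, on extending the general nonparametric and .05 rule to fidelity, and on two-sided testing. It is a secondary point about an ancillary check in a pilot trial. It does not touch the primary outcome analysis.

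**What to change.** Remove *significantly* from both expectations in the Fidelity section. Report the coded sessions descriptively, listed by participant and arm: global ratings against the plan's own threshold of 4 or higher, reflection-to-question ratio, and information-giving counts. State how many sessions per selected participant were coded, and that two participants per arm give an indication of delivery and not a test.

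The cost is wording and a small table. No further coding is needed. The Results section says testing was completed in mid-November 2019, but the change can still be made in the analysis and report. If a test is wanted instead, at least four participants per arm would have to be coded and the unit of analysis stated. The article does not say whether recordings exist for that.

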### Statistical Analysis

Descriptive statistics will be used to summarize the characteristics of the GOPCs and participants with regard to baseline characteristics and patterns of mean change over time. The primary analysis will examine the changes in HbA_1c_ at the 6- and 12-month follow-ups in comparison to the baseline. Secondary analyses will include all clinical, psychosocial, and self-care measures that are continuous outcomes. For data analyses, SPSS (IBM Corp, Armonk, NY) will be used. As this is a pilot study, nonparametric statistical tests will be used. The baseline values will be reported as means (SD). A *P*-value<.05 will be regarded as statistically significant.

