### Subjects

#### Inclusion Criteria

Patients are eligible if they were diagnosed as having type 2 DM for at least 1 year and are 18 to 65 years of age with poor DM control (defined as HbA_1c_≥8). Patients who have or have not received maximum dosages of oral hypoglycemic agents are equally eligible.

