### Hypotheses

Our hypotheses are that MI can reduce HbA_1c_ levels, improve clinical and psychosocial outcomes, and increase diabetes self-care when compared with patients’ usual care.

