### Recruitment Procedure

The patients will be informed while participating in the NLC. Advanced practice nurses (APNs) will assist participants in achieving the primary goal of treatment for HbA_1c_ levels less than 7.0%, which is the target defined by the Manual for Risk Assessment and Management Programme (Diabetes Mellitus) in the Primary Care Setting under the Hospital Authority of Hong Kong. This primary goal is applicable for both groups in the study.

After randomization, all outcome measures will be assessed at baseline, 6 months, and 12 months in both groups. Randomization is generated by a research randomizer with a 1:1 allocation ratio in both groups. Each GOPC is considered as a single unit of randomization.

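### The primary analysis names baseline as its only comparator and should state the MI versus usual care contrast that the hypotheses require

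*Protocol article*

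**What the plan says.** The Statistical Analysis section defines the primary analysis in one sentence, as a look at HbA1c changes "at the 6- and 12-month follow-ups in comparison to the baseline". Two further sentences bear on inference: "As this is a pilot study, nonparametric statistical tests will be used", and a P "value<.05 will be regarded as statistically significant". The section does not mention arms, MI or usual care, and it does not say whether the nonparametric tests are paired or two-sample.

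The question posed elsewhere is comparative. The Hypotheses section expects MI to lower HbA1c, improve other outcomes and "increase diabetes self-care when compared with patients’ usual care". The Abstract and the Objectives section also set MI against usual or normal care, and the Impact section speaks of showing which of two methods works better.

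Two design features matter here. Under Inclusion Criteria, patients "are 18 to 65 years of age with poor DM control", defined as HbA1c of 8 or more. Under Recruitment Procedure, nurses work towards HbA1c below 7.0%, and "This primary goal is applicable for both groups in the study".

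**The concern.** The comparator in the stated primary analysis is not the comparator in the hypothesis. A test of follow-up against baseline within the MI arm answers whether HbA1c changed, not whether MI changed it more than usual care did.

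This trial is exposed to the difference because entry depends on a high value of the primary outcome itself. Some fall on remeasurement can therefore occur with no treatment effect, and care common to both arms may add to it. A significant fall in the MI arm could then be reported as the primary result in favour of MI. The pattern of a significant fall under MI and none under usual care could be reported the same way, although it is not evidence of a difference between arms.

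A condensed article may leave the choice of test, covariates and missing-data method to a fuller plan. What the primary analysis compares is different: the article does state it, and in words that do not match its own hypothesis.

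**Working it through.** The article gives no figure to reproduce on this point. It gives no SD, HbA1c distribution or retest correlation, so everything below except the threshold, arm size, anticipated effect and ICC is assumed.

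**Inputs from the article.** Entry threshold 8 (Inclusion Criteria); 20 to 25 patients per arm, anticipated effect 0.32 points and ICC 0.05 (Sample Size Calculation); significance at P<.05 (Statistical Analysis; two-sided assumed).

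**Assumed.** Clinic HbA1c is normal with mean 7.3 and SD 1.2. Correlation ρ between baseline and follow-up is 0.6 to 0.9. The true MI effect is zero.

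**Case A: the qualifying value is also the baseline.**

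- Standardised threshold: a = (8 − 7.3)/1.2 = 0.583.
- Mean of those selected: 7.3 + 1.2 × φ(a)/(1 − Φ(a)) = 7.3 + 1.2 × 0.3365/0.2798 = 8.74.
- Expected fall from regression to the mean: (1 − ρ) × (8.74 − 7.3) = (1 − ρ) × 1.44.

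| ρ | Expected fall | Fall ÷ 0.32 | Signed-rank rejection, n = 20, simulated |
|---|---|---|---|
| 0.6 | 0.58 | 1.8 | about 68% |
| 0.7 | 0.43 | 1.4 | about 53% |
| 0.8 | 0.29 | 0.9 | about 37% |
| 0.9 | 0.14 | 0.45 | about 20% |

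In the same simulations, a significant fall under MI with none under usual care appears in 16–24% of null trials.

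**Case B: the baseline is a separate, later sample.** If all three samples correlate equally (0.6 to 0.8), the qualifying value predicts baseline and follow-up equally well. The expected fall is then 0 and the signed-rank test rejects in about 4–5% of trials. If the qualifying value correlates 0.1 more with baseline than with follow-up, rejection is about 9–12%; if 0.2 more, about 19–25%.

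**Fall common to both arms.** The article does not quantify one. For illustration, adding 0.3 points to both arms in Case A (n = 20) raises within-arm rejection to 91–96%.

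**Between-arm contrast.** A Mann-Whitney test on change, MI against usual care, rejects in 3.7–6.0% of null trials over all Case A scenarios run (mean/SD 7.3/1.2 and 7.5/1.5; n = 20 and 25; with and without the common fall). Those runs contain no clinic effect.

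**Adding the clinic effect.** Each clinic is a single unit of randomization, so there is one clinic per arm. With ICC 0.05 applied to the analysed outcome, the design effect is 1 + (20 − 1) × 0.05 = 1.95 at 20 per arm and 1 + (25 − 1) × 0.05 = 2.20 at 25. The true standard error is therefore about √1.95 = 1.40 to √2.20 = 1.48 times the patient-level one. In simulation, a nominal 5% patient-level Mann-Whitney test rejects in about 16% (n = 20) to 18% (n = 25) of null trials.

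**The case against.** **The sentence defines a change score.** This is the strongest reply. A two-arm trial often describes its outcome as change from baseline and then compares that change between arms. The objectives and hypotheses point that way, and both arms have the same assessments. No paired test is named, and no rule says that a fall in the MI arm counts for MI. A reader might infer that the plan replaces the comparison with usual care by a before-after test. The documents do not support that: the text is ambiguous. What stands is that the only comparator named is baseline and a significance rule follows, so the within-arm reading is open to anyone who applies the section literally.

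**The large false-positive rates need the qualifying value to be the baseline.** This is right, and the article leans the other way. Invitations go down a list of people already known to be eligible, and baseline is assessed after randomization at a health check with fasting bloods. That suggests a separate sample without establishing it. The 20–68% range is therefore conditional.

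**The shared treatment target need not cause a new fall.** It is an existing programme target, patients were diagnosed at least a year earlier, and medical treatment is not part of the intervention. It is fair to say that such a fall is possible and unquantified, and not that it is established.

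**One clinic per arm spoils the between-arm contrast as well.** True, and naming the contrast does not cure it. But dropping the contrast would discard the only control the design has.

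**It is a pilot.** The article says so and acknowledges its small sample. That lowers the severity; it does not make a before-after test informative about MI.

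**Conclusion.** The point holds as an ambiguity with a consequence: the stated primary analysis does not name the contrast that the hypotheses need, and its literal wording allows within-arm tests that cannot separate MI from selection or common care. It should be fixed.

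The size depends on a fact the article does not give. If the qualifying HbA1c is the baseline, a null trial shows a fall of about 0.14–0.58 points and a significant within-arm test in about 20–68% of cases, under mean 7.3, SD 1.2, correlation 0.6–0.9 and 20 patients. With a separate baseline and equal correlations, the rate is about 5%. Any fall from care common to both arms would come on top in either case.

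It would also be wrong to infer that a between-arm test restores a 5% error rate. It does so only without clinic variation; at the article's own ICC of 0.05 the rate is about 16–18%.

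**What to change.** Reword the primary analysis as follows:

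- The primary analysis is the difference in HbA1c between arms (MI minus usual care) at one named follow-up time, adjusted for baseline HbA1c.
- Name the method, for example ANCOVA or a rank-based equivalent, and reconcile it with the sentence that prescribes nonparametric tests.
- Report the result as an exploratory estimate with a 95% CI. State that with one clinic per arm the arm effect cannot be separated from the clinic effect, and that a patient-level interval ignores clinic variation and is too narrow.
- Show within-arm changes descriptively, without P values, and draw no conclusion about MI from them.
- Say whether the baseline HbA1c is the qualifying value or a separate sample.

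The choice between 6 and 12 months is the investigators' to make, and should be recorded before the arms are compared. The Results section says that testing is complete and results are still to be published, so this is a change to the analysis text and the reporting. It takes a few sentences and no new data; the cost is giving up a confirmatory P value, which the two-clinic design could not support.
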